### Interventions

#### CETA

CETA is a transdiagnostic mental health intervention developed for delivery by non-professionals in LMIC (Murray *et al.*
2014). The development of CETA (Table 1) was based on research of common elements or transdiagnostic treatment approaches used in the USA (Chorpita & Daleiden, 2009; Farchione *et al.*
2012; Weisz *et al.*
2012), but with a focus on being appropriate for training and delivery by non-professional (i.e. lay providers) in lower resource settings (Murray *et al.*
2014). CETA is not a ‘new’ treatment but rather an *approach* that teaches CBT elements common to evidence-based treatments (Chorpita *et al*. 2005) for trauma, anxiety, depression, and behavioral problems. As a CETA, this approach allows a counselor to flexibly decide on what element(s), order, and dose are needed depending on presentation.

**Table 1. tab01:** Components of CETA

Component	Simplified name (used in training)	Description
Psychoeducation and engagement	Introduction	Focus on obstacles to engagement Linking program to assisting with client's problems Includes family when appropriate Program information (duration, content, expectations) Normalization/validation of current symptoms/problems
Anxiety management strategies	Relaxation	Strategies to improve physiological stress Examples include: deep breathing, meditation, muscle relaxation, and imagery. Others added by local cultures
Behavioral activation	Getting active (GA)	Identifying and engaging in pleasurable, mood-boosting, or efficacy-increasing activities
Cognitive coping/restructuring	Thinking in a different way – part I and part II (TDW1 and TDW2)	Understand association between thoughts, feelings, and behavior Learn to restructure thinking to be more accurate and/or helpful
Imaginal gradual exposure	Talking about trauma memories (TDM)	Facing feared and avoided memories in detail Gradual desensitization/exposure
In vivo exposure	Live exposure	Facing innocuous triggers/reminders in the client's environment Gradual desensitization/exposure
Suicide/homicide/danger assessment and planning	Safety	Assessing client risk for suicide, homicide, and domestic violence Developing a focused plan with the client and client's family (when appropriate) Additional referral/reporting when needed
CBT for substance use and relapse prevention	Substance use element (SU)	Utilizes motivation and CBT principles and activities to get client buy-in and alter behavior patterns to change substance use/abuse behavior
Safety planning and violence prevention	Safety and violence prevention	Walks through detailed safety plans specific to IPV Discusses behavioral or situational modifications that may help prevent violence

CETA was chosen as the intervention due to its evidence base and its modular transdiagnostic design. CETA is currently the only transdiagnostic model with two rigorous clinical trials in LMIC that each show strong effect sizes across a range of symptoms: (a) on the Thailand/Myanmar border with Myanmar refugees (*N* = 347; ES: 1.19 post-traumatic stress, 1.16 depression, 0.79 anxiety) (Bolton *et al*. 2014) and (b) in Southern Iraq with survivors of conflict, torture, trauma, and ongoing stressors (*N* = 149; ES: 2.40 post-traumatic stress, 1.82 depression, 1.60 anxiety) (Weisz *et al*. 2015). These findings provide some evidence of effectiveness for CETA with adults, as well as ability of lay providers to learn this type of modular, flexible approach. In Ethiopia, results showed significant decreases in symptoms of internalizing (*d* = 1.37), externalizing (*d* = 0.85), and post-traumatic stress (*d* = 1.71) symptoms, and improvements in well-being (*d* = 0.75) (Murray *et al.*
under review). The modular nature of CETA allowed us to develop and adapt the elements and flows to fit our study population.

For this study, CETA was originally planned and initially implemented as a group treatment. Groups were set up to be specific to one participant type (i.e. men, women, or children) and composed of 5–7 individuals. Group assignment was based on the participants’ language, residence, and age (for youth groups). Each group was run by two trained providers pre-paired based on language fluency and location. Specifically, counselors were not allowed to work in or near the neighborhoods where they reside to reduce counselor bias and ensure client anonymity. Groups were designed to run for 90–120 min, with each session beginning with a tea time where participants could socialize to promote group cohesion and motivate regular and punctual attendance. Delivery of CETA included varying elements and ‘dose’ of elements (i.e. the number of sessions or time spent on it) depending on clients’ symptoms, with a suggested 6–12 weekly sessions depending on need. Figure 2 shows a common flow for the men's, women's, and children's group with comments on what might be added for flexibility based on need.

**Fig. 2. fig02:**
[figure not shown]
Most common flow of CETA intervention elements with possible modifications.

CETA was adapted for this trial to include a CBT-based substance use (SU) reduction element. CBT for SU disorders has demonstrated efficacy as both a mono-therapy and as part of combination treatment strategies (McHugh *et al.*
2010). Evidence from numerous large-scale trials and reviews support the efficacy of CBT for alcohol and drug use disorders (Dutra *et al.*
2008; Magill & Ray, 2009). Typically, CBT for SU includes any or a combination of the following: (a) motivational enhancement strategies, which target ambivalence to behavior change related to substances (Miller & Rollnick, 2013); (b) contingency management approaches, which work on countering the reinforcing effects of substances and providing positive reinforcements tied to non-using decisions; (c) relapse prevention, which applies a functional analysis of personalized SU cues (e.g. places, smells, people, etc. that promote urges to use) and implementation of alternative/competing responses to these cues.

Two authors drafted the SU element ([name] and [name]), which was then reviewed by other CETA trainers, SU treatment experts, and local counselors from Zambia who had provided other CBT treatments (i.e. trauma-focused CBT; Murray *et al.*
2015). Within the CETA SU element, there were motivational statements, including asking participants at multiple time points throughout the session to determine a behaviorally specific goal and rate their motivation to complete that goal. Adapted from other empirically supported SU treatments (Henggeler *et al.*
2002; Danielson *et al.*
2012), this component also includes helping participants identify all of the drivers that underlie their drinking behavior (e.g. boredom, passing the bar on their way home, coping with stress). Specific interventions and strategies that counter this list of individualized reasons listed (e.g. behavior replacement, avoidance) are then taught to the participants and practiced. The session is completed with revisiting the individual goals and the motivation to work toward or complete that goal. This component was designed in the context of this study to be delivered to all men, and also any women who also reported substance abuse.

Since our population of interest was the family unit, and our primary outcome is prevention of violence (which commonly co-occurs with SU; Widom & White, 1997) our team also developed a ‘SU support’ element that was delivered to the women when applicable. Utilization of a family support system, including family-based approaches, has been shown to be an efficacious approach to decreasing SU and relapse in other populations (Waldron & Turner, 2008). In CETA, the SU support element is designed to: (a) provide psychoeducation about the SU to the partner of the substance abuser, (b) to have the partner help in identifying the user's drivers (e.g. why the participant uses), and (c) to help the partner identify ways in which she can support the reduction of use (e.g. plan activities that are not at a bar, offer a favorite dinner with a beer at home).

The apprenticeship model of training and supervision is being used to deliver CETA (Murray *et al*. 2011). A 10-day in-person CETA training was conducted by study authors ([name] and [name]), followed by weekly small group meetings in which lay counselors practiced the treatment elements with a local supervisor (before providing CETA to clients). Sixty-three lay counselors (20 male, 43 female) and seven supervisors (3 male, 4 female) between the ages of 20 and 60 years (average age 33.7 years) were trained in February and March 2016. Supervisors of CETA completed one pilot treatment group to strengthen their skills and understanding of the components decision-making process and CETA treatment. Counselors continue to meet in small groups and receive supervision on each case throughout the study. Weekly meetings are also continuously held between each local supervisor and a CETA trainer ([name] in person, [name] via skype) for 2–3 h to either review group role-plays or discuss CETA cases.

#### Treatment as usual

The control condition is defined as TAU. In Zambia, no formal services or standard of care exists for IPV or alcohol use problems. There are some organizations that provide services such as informal counseling from parish priests, church officials, or other community leaders. At the beginning of the study, all participants were provided a list of relevant services in Lusaka. We did not exclude any families based on having received these types of services and do not in any way dissuade families from accessing these types of services or information during the study.

### Assessment of outcomes and follow-up

Post-assessments were conducted with participants starting in October 2016 and are ongoing. All post-assessments (4/5, 12, and 24 months post-baseline) are conducted in the same format (i.e. ACASI), and at the same locations as baseline. At baseline and all follow-up visits, participants are provided with reimbursement for travel. The primary outcome in the study is violence as measured by the SVAWS. Secondary outcomes include alcohol and other SU, mental health, psychological violence, and gender norms. Each participant type (woman, man, child) completes a specific battery of instruments via ACASI. The measures included in ACASI were pilot tested with participants sampled from the same source population as those in the trial to check translation accuracy and item comprehension. In addition to the self-report measures administered via ACASI, a hair sample is collected from participants as a biomarker of chronic stress (Russell *et al.*
2012). The full list of outcome instruments is displayed in Table 2.

**Table 2. tab02:** Primary and secondary outcome measures for VATU trial

				Cronbach's *α*^a^		
Measure	Construct	Reference	Description	Woman	Man	Child
Primary outcome						
Severity of Violence against Women Scale (SVAWS)	Violence	Marshall (1992)	46 items assessing how often (never, once, a few times, many times) a current partner perpetrated acts of violence against the participant in the past year. Subscales include: (a) threats of violence; (b) physical violence; and (c) sexual violence. Previously used in a study of IPV among women with partners who have alcohol abuse in South Africa (Peltzer & Pengpid, 2013)	0.95	–	–
Secondary outcomes						
World Health Organization IPV measure (WHO-IPV)^b^	Violence	World Health Organization (2005)	Nine items assessing how many times a current or previous partner ever and recently perpetrated acts of violence (never, once, a few, many). Previously used in the WHO multi-country study on Women's Health, including in Tanzania and Namibia	0.95	0.96	–
Youth Victimization Scale (YVS)	Violence	Nadel *et al*. (1996)	135 items assessing how often (never, once, sometimes, often) youth have experienced various types of recent violence at school, in the neighborhood, and at home	–	–	0.98
Alcohol Use Disorders Identification Test (AUDIT)^c^	Alcohol	Saunders *et al.* (1993)	10 items assessing hazardous alcohol use. Scores of ⩾3 for women and ⩾4 for men are considered hazardous. Previously validated in Zambia (Chishinga *et al.* 2011)	0.88	0.85	–
Alcohol, Smoking, and Substance Involvement Screening Test (ASSIST)	Drug use	Humeniuk *et al.* (2008)	Seven items assessing frequency and consequences of use for a range of substance types. Previously validated in Zambia (Kane *et al.* 2016*a*)	0.97	0.97	0.98
Center for Epidemiological Studies-Depression Scale (CES-D)	Depression	Radloff (1977)	20 items assessing frequency of depression symptoms over the past week (never, 1–2, 3–4, 5–7 days). Previously validated in Zambia (Chishinga *et al.* 2011)	0.92	0.90	–
Youth Self Report	Mental/behavioral health	Achenbach (1991)	112 items assessing occurrence of child mental health symptoms and behaviors in the past 4 weeks. Response options are: not true, sometimes true, very true. Subscales assess internalizing symptoms and externalizing behaviors. Validation study among adolescents in Zambia currently underway as part of an ongoing study (clinicaltrials.gov # NCT02054780)	–	–	0.98
Harvard Trauma Questionnaire (HTQ)	Trauma/post-traumatic stress disorder (PTSD)	Mollica *et al.* (1992)	17 items assessing lifetime experience of a range of traumatic events. 39 items assessing symptoms of post-traumatic stress in the past week (not at all, a little, quite a bit, extremely)	0.96	0.95	–
Child PTSD Symptom Scale (CPSS)	Trauma/PTSD	Foa *et al*. (2001)	14 items assessing lifetime experience of a range of traumatic events. 17 items assessing symptoms of post-traumatic stress in youth in the past 2 weeks (never, once in a while, more than half the time, almost always). Validation study among adolescents in Zambia currently underway as part of an ongoing study (clinicaltrials.gov # NCT02054780)	–	–	0.93
Aggression Scale	Aggression	Orpinas & Frankowski (2001)	11 items assessing frequency (range of 0 times to 6+ times) of youth aggressive behaviors over the past week	–	–	0.87
Gender Equitable Men's Scale (GEMS)	Gender norms	Pulerwitz & Barker (2007)	24 items assessing the degree to which adult participants agree (agree, partially agree, do not agree) with statements on gender norms	0.88	0.89	–
Index of Psychological Abuse (IPA)	Psychological violence	Sullivan & Bybee (1999)	33 items assessing how often a partner perpetrated psychological abuse over the past 3 months (never, rarely, sometimes, often)	0.94	–	–
Hair sample for cortisol biomarker	Chronic stress	Henley *et al.* (2013)	–	–	–	–

a Cronbach's *α* calculated from all available baseline data

b The woman reports *experiencing* violence and the man reports *perpetration* of violence on the WHO-IPV measure

c Participants complete two versions of the AUDIT; one in reference to their own alcohol use and one in reference to their partner's alcohol use

In addition to the primary assessment time points, participants are tracked weekly during the intervention phase. For CETA participants, counselors administer a brief symptom monitoring form and the Alcohol Timeline Followback (TLFB; Sobell & Sobell, 1992) at each session. Additionally, the Short Inventory of Problems (SIP; Tonigan & Miller, 2002), which measures consequences associated with alcohol misuse, is administered at the first and last CETA session. Control participants receive weekly phone calls or home visits from our research staff to assess safety during the intervention period and complete the Alcohol TLFB and brief symptom monitoring form monthly. Following the first ACASI post-assessment, both control and intervention participants receive monthly safety check-in phone calls from the research team.

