2012). Women whose husbands frequently return home drunk have an increased risk of experiencing abuse (Abramsky *et al.*
2011; Fulu *et al.*
2013). The role of alcohol use in IPV perpetration and experience is a particular concern in low- and middle-income countries (LMIC), specifically in sub-Saharan Africa, where rates of problematic alcohol use are increasing (Shield *et al.*
2013). Mental health problems, particularly depression and post-traumatic stress disorder, have also been associated with experiencing (Iverson *et al.*
2011; Kuijpers *et al.*
2012) and perpetrating (Fulu *et al.*
2013; Oram *et al.*
2014) violence.

Economic and social ‘structural’ interventions have demonstrated effectiveness for addressing some risk factors (e.g. inequitable gender norms) of violence, but findings for actual reductions in its occurrence are mixed (Bourey *et al.*
2015). Although these structural interventions are essential to broad primary prevention of IPV, the complex inter-relationship between violence, alcohol, and mental health suggests a need for integrated approaches that include treatments targeting high-risk groups (Guedes *et al.*
2016). Two trials conducted in the USA suggest cognitive–behavioral therapy (CBT) interventions and alcohol treatment combined with violence prevention programs show promise for impacting some types of IPV (Tirado-Muñoz *et al.*
2014; Wilson *et al.*
2014). Given the high rate of IPV in LMIC and the dearth of evidence-based interventions in these settings, more studies are needed to evaluate approaches that address high-risk families affected by IPV, alcohol use, and/or mental health problems.

This paper describes: (1) the process of adapting an evidence-based, modular transdiagnostic treatment approach (common elements treatment approach; CETA) (Murray *et al.*
2014) to address violence and alcohol abuse, and (2) the protocol for testing CETA in an ongoing randomized controlled trial. The trial is part of a larger consortium of studies, the *What Works to Prevent Violence Against Women and Girls Programme* (http://www.whatworks.co.za/), investigating the underlying causes of VAWG and strategies for prevention in LMIC. The primary aims of the trial are to evaluate the effectiveness of the adapted CETA intervention on (a) reducing and preventing women's experience of IPV and (b) reducing male partner's hazardous alcohol use.

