### Eligibility screening

Families who expressed interest in the study were invited to participate in an eligibility screening at a later date, typically within 1 week, at a site in their community (i.e. school, church, or community center). Study assessors met with families privately and provided a brief overview of the purpose and procedures of the study to all family members (i.e. the woman, man, and child). Informed consent was then obtained with each family member separately in a private space. Consent was obtained for all study activities (screening, assessments, and intervention).

Following informed consent, the woman and her male partner separately completed an eligibility screener. For women, this consisted of the Severity of Violence Against Women Scale (SVAWS; Marshall, 1992), for assessing recent IPV; and the Alcohol Use Disorders Identification Test (AUDIT; Saunders *et al.*
1993), for measuring her report of her partner's hazardous drinking. Men only completed a self-reported AUDIT. To be eligible, (a) the woman had to report recent (past 12 months) experience of at least a moderate level of violence (SVAWS physical violence subscale score of ⩾38) and (b) she or her partner had to report that he has engaged in hazardous alcohol use (AUDIT score of ⩾8). Additional eligibility criteria are detailed in Box 1.
Box 1.Inclusion and exclusion criteria for the VATU trial.Inclusion criteria
The family must live in one of the three study compounds in Lusaka (i.e. cannot only be staying temporarily).All family members must speak at least one of the three study languages: English, Bemba, or Nyanja.The family must consist of an adult (aged 18 years or older) female and adult male in a relationship (i.e. married or dating). In addition, the woman has the choice (if applicable) to identify one of her children between the ages of 8 and 17 for inclusion in the study.Both the adult female and her male partner must provide consent. For one of her children to also participate, the woman's permission and the child's assent are required.The adult female must score 38 or more on the Severity of Violence Against Women Scale (SVAWS; physical violence subscale) indicating experience of at least a moderate amount of intimate partner violence.The adult male must have a score of 8 or higher on the Alcohol Use Disorders Identification Test (AUDIT) as reported by himself or his partner, indicating that he drinks alcohol at hazardous levels.Exclusion criteria

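### The protocol gives two unexplained AUDIT cut-offs for hazardous male drinking, and makes alcohol a primary aim but only a secondary outcome

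*Protocol article*

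**What the plan says.** **Definition of hazardous use.** Under Eligibility screening, "she or her partner had to report that he has engaged in hazardous alcohol use (AUDIT score of ⩾8"; Box 1 repeats the threshold of 8. Table 2, under Assessment of outcomes and follow-up, describes the 10-item AUDIT and states: "Scores of ⩾3 for women and ⩾4 for men are considered hazardous".

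**Status of alcohol.** The Background says "The primary aims of the trial are to evaluate the effectiveness of the adapted CETA intervention on" two things, the second being "reducing male partner's hazardous alcohol use". The outcome section says "The primary outcome in the study is violence as measured by the SVAWS", followed by "Secondary outcomes include alcohol and other SU, mental health, psychological violence, and gender norms". The sample size (Data analysis) and the 12-month stopping rule (Data and safety monitoring) rest on SVAWS alone.

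**Form of the alcohol analysis.** Data analysis provides linear mixed models for continuous outcomes and generalized linear mixed models for binary ones, and does not say which applies to AUDIT. It speaks of modelling outcome scores, with the baseline score included only if the arms differ meaningfully at baseline. Table 3 reports AUDIT as mean (SD). Footnote c to Table 2 says that each participant completes one AUDIT about their own drinking and one about the partner's. The article does not say which of these measures the male outcome.

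**The concern.** One label on one instrument carries two thresholds. A man who enters at 15 and ends at 6 is below the entry threshold but still hazardous by Table 2. Aim (b) is worded as a reduction in hazardous use, and the article gives that term a numerical meaning only through a threshold. AUDIT is also the only instrument in Table 2 that is given a score cut-off, so a later analyst could reasonably turn it into a binary outcome and would find two candidate definitions.

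The second conflict concerns the claim. A primary aim normally has a primary outcome and a sample size. Aim (b) has neither, so a later report could present the alcohol result as primary by citing the Background, or as secondary by citing the Methods.

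**Working it through.** **The plan's own figure.** There is none for AUDIT. The stated 50 families per arm is for the SVAWS physical violence subscale. It corresponds to a standardised difference of √(2/50) × (1.960 + 0.842) = 0.56. The planning mean and SD come from a cited study and are not given, so the 50 can be neither reproduced nor refuted. It does not bear on alcohol.

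**Inputs.** Male self-reported AUDIT at baseline is 15.8 (SD 10.4), from Table 3. The final sample is 248 families randomized 1:1, so 248/2 = 124 per arm.

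**Assumptions.** No dropout and no change in controls. The treated mean falls by a given percentage. For the proportions, the treated SD shrinks in the same ratio; for the score, a common SD of 10.4 is kept. Scores follow a normal curve or, because the normal curve puts Φ(−15.8/10.4) ≈ 6% of men below zero, a beta curve on an assumed range of 0 to 40 with the same mean and SD.

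**Share of men at or above cut-off c (normal case)** = 1 − Φ((c − 0.5 − mean)/SD).

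- Baseline, c = 8: (7.5 − 15.8)/10.4 = −0.798, giving 78.8% (beta 72.8%).
- Baseline, c = 4: (3.5 − 15.8)/10.4 = −1.183, giving 88.2% (beta 86.9%).
- After a 30% fall (mean 11.06, SD 7.28), c = 8: (7.5 − 11.06)/7.28 = −0.489, giving 68.8% (beta 62.2%).
- After a 30% fall, c = 4: (3.5 − 11.06)/7.28 = −1.038, giving 85.0% (beta 84.6%).

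**Power for proportions** = Φ((d − 1.96 × SE0)/SE1), where d is the risk difference, SE0 the pooled and SE1 the unpooled standard error with 124 per arm. Normal case, 30% fall:

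- c = 8: d = 0.100, SE0 = 0.0559, SE1 = 0.0555, power 43%.
- c = 4: d = 0.031, SE0 = 0.0433, SE1 = 0.0432, power 11%.

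**Power for the score**, 30% fall: difference 0.3 × 15.8 = 4.74; SE = 10.4 × √(2/124) = 1.321; Φ(4.74/1.321 − 1.96) = Φ(1.63), about 95%.

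| Assumed fall | Difference and power at ≥8 | Difference and power at ≥4 | Power on score |
|---|---|---|---|
| 20% | about 6 points, 16–18% | 1–2 points, 4–6% | 67% |
| 30% | 10–11 points, 43% | 2–3 points, 8–11% | 95% |
| 50% | 26–27 points, 99% | 8–9 points, 41–46% | about 100% |

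Ranges span the normal and beta cases. The cut-off has a large effect on a binary analysis and none on the score analysis.

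**The case against.** The strongest reply is that no binary AUDIT endpoint exists in the article. The Table 2 cut-off sits in an instrument description, the model section speaks of scores, and Table 3 gives a mean and SD. An enrolment threshold may also legitimately be stricter than a scale's own cut-off. All of this stands. A reader might infer that the alcohol conclusion depends on an unfixed cut-off; the article does not support that, because on the score no cut-off is used. What remains is that both numbers are presented as the meaning of hazardous, without explanation.

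The status of the outcome is also settled. SVAWS is the sole primary outcome wherever outcomes are defined, and alcohol is explicitly secondary. The outlier is the Background sentence on primary aims. A reader might go on to infer uncontrolled type I error: two independent primary tests at 0.05 would give 1 − 0.95² = 9.75%. That needs a second primary test, and none is planned. A testing order among secondary outcomes is commonly left to the full protocol or SAP, which is not shown, so its absence is not a finding.

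Entry on either partner's report suggests a floor problem too. Under the two assumed curves, 21–27% of men would start below 8 on self-report and could not leave the hazardous group at that cut-off. This again presumes a binary self-report outcome at 8, which is not stated; partner-reported AUDIT is collected as well.

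**Conclusion.** Two inconsistencies hold as a matter of text: two unexplained definitions of hazardous male drinking on one instrument, and a primary aim whose outcome is secondary and has no sample size of its own. Neither affects the primary SVAWS result or its error rate.

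The cut-off would affect the alcohol conclusion only if AUDIT were dichotomised. In that case, for a 30% fall, the choice of threshold moves power between about 43% and 8–11%, against about 95% on the score. Those figures rest on assumed distributions, assumed effects and complete follow-up; dropout would lower all of them. The full protocol or SAP may already fix the form of the analysis, but the contradictions within the article remain until its wording is aligned.

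**What to change.** 1. State that the male alcohol outcome is the AUDIT analysed as a continuous score, and name whose report is used, his own or his partner's.
2. Always adjust for the baseline AUDIT score, rather than only when the arms are judged to differ. This removes a data-dependent choice and costs one model term.
3. Reconcile the Eligibility screening section and Box 1 with Table 2, or explain why they differ. If a supportive binary analysis is kept, use a single definition, fixed before unblinding.
4. Reword aim (b) as a secondary aim, so that SVAWS alone carries the primary claim.

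All four are wording changes; they need no new data and no change to recruitment or follow-up. The downside is that the alcohol result can be claimed only as a secondary finding. If the investigators want two primary claims instead, the error rate across both would have to be addressed, and aim (b) would need its own sample size justification.
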